**Fig. 1 fig1:**
[figure not shown]
Schematic representation of the experimental protocol.

**Fig. 2 fig2:**
[figure not shown]
Schedule of enrolment, interventions, and assessments, according to the SPIRIT guidelines.

### Data management

2.5

All participants will be assigned a unique identifier to protect they identify. All personal data will be stored in encrypted files with access restricted to the main researcher. Original paper files will be stored in secure, locked cabinets onsite. All data will be inserted electronically. Data will be double-checked for errors at the time of entry, with all changes performed being documented. Additional findings will be performed through statistical software. Data ranges and consistency checks will be performed for data integrity. No specific auditing procedures are planned for this trial. The results will be fully disseminated in peer-reviewed scientific journals and conferences.

### Adherence promotion efforts

2.6

To increase adherence and promote the compliance of participants in the familiarization session and in each one of the 2 experimental trials, different strategies will be adopted namely logistical support (compensation for travel reimbursement) and collaboration between subjects and research staff (with regular phone calls and messages with positive reinforcement). Also, in the day before the familiarization session and the 2 experimental trials, the researchers will reach participants by phone, to gently remind them of the importance of participating in the study.

### Statistics

2.7

Statistical analysis will be performed using IBM SPSS statistics version 27.0, 2020 (SPSS Inc., an IBM Company, Chicago, IL, USA). To test the normality of distribution of the variables, the Shapiro-Wilk test will be performed. Baseline demographic and clinical characteristics of the participants will be analysed using descriptive statistics (mean, standard deviation, and range). For the continuous normal distributed variables, the one-way repeated measures analysis of variance (ANOVA) will be used to assess the association between the intervention and the perceptual, physical and physiological responses (thermal sensation, thermal comfort, perceived thirst, HR, accelerometery data, Tcore, SR, *ad* libitum fluid intake, lactate and glucose blood levels). Single time-point data will be examined for within-group effects across conditions using a one-way ANOVA. A two-way analysis repeated measures ANOVA will be used to test for within-group effects across time in both conditions. Missing data will not be included in the statistical analysis. Participants who discontinue or deviate from intervention protocols, and who meet exclusion criteria at some point of the intervention period, will be excluded. A *p* value of 0.05 will be considered statistically significant. Data will be reported according to the guidelines of consolidated standards of reporting trials (CONSORT) [28].

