### Sample size and recruitment

2.1

For sample size and statistical power calculations, power analysis was based on changes in TS after the internal administration via mouth-rinsing or ingestion of menthol solution. Considering a type I error of 5% and a power of 90%, with a statistical significance (p-value ≤0.05) and a moderate effect size of 0.54 (differences in TS were considered following Jeffries and Waldron results [30]), a total of 10 participants will be needed (using G*Power 3.1.9.2 ®). Considering a drop-out rate of 30% throughout the study, 13 participants as a buffer against attrition.

The Portuguese Football Federation (PFF) will contribute by recruiting referees through direct contact, databases, and referral sources. Following an initial telephone screen to determine the eligibility of potential participants, an orientation session (introductory meeting) will be scheduled to offer detailed information about the study, including the number and type of assessments, the length and nature of the exercise training, and the time commitment required to complete the study. After eligibility criteria confirmation, all participants will sign an informed consent form before being allocated to the study. Participants’ privacy and confidentiality will be guaranteed during and after investigation according to the Portuguese data protection law. Privacy, anonymity, and confidentiality of data/information identifying the participants will be strictly maintained. All information and results of the tests performed on the participants will be confidential. No one other than the investigators of this research will have access to the data.

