##### Blood lactate and glucose levels

2.4.6.8

Blood lactate and glucose levels will be measured before and after the protocol, recurring to a Blood Lactate Meter (Lactate Pro 2, Arkray, U.S.A) and a Glucometer (FreeStyle Precision Neo, Abbott Laboratories, U.S.A), respectively. Both devices have been previous validated [42,43].

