#### Experimental trial protocol

2.4.7

The protocol of the trial will be divided into 39 phases (T1-T39) (Table 1 and Fig. 1). The participants will arrive at the testing facilities 1 h before the start of the warm-up. Schedule of the enrolment, interventions, and assessments is described in Fig. 2.

**Table 1 tbl1:** Description of the experimental trial phases.

**T1**	BodyCap® will be ingested by the participant.
**T2**	Then, participant's 24-h food recall diary will be collected.
**T3**	Hydration status will be assessed, after urine collection.
**T4**	After voiding their bladder, body mass will be measured on a digital platform scale, weighted with minimal clothing. Individual marked drink bottles will be distributed to the referee so that fluid consumed at “water breaks” may be recorded via the measurement of body mass changes. Participants will be informed that they may drink water *ad libitum*, on “water breaks”.
**T5**	Lactate and blood glucose levels are now going to be measured.
**T6**	Devices for assessing HR and physical performance parameters will now be placed on the referee and synchronized.
**T7**	TC, PT and TS are will be measured.
**T8**	Beverages (previously prepared and stored at the intended temperature) will be distributed to the referee. Total amount of beverages for pre-cooling previously described (75 ml of beverage A or B) will be divided into 3 equal parts and made available to the participant every 1 min. Beverages temperature will be monitored with a digital thermometer, to the nearest 0.1 °C (Proficook, Germany). The entire cooling stage will be carried out at a mild temperature of 18–20 °C, at rest. Participants will be instructed to swill both beverages for 10-s before spitting into a bowl without swallowing. The first 1/3 of the 75 ml of beverage will be administered.
**T9**	TC, PT and TS will be again evaluated.
**T10**	The second 1/3 of the 75 ml of pre-cooling beverage will be distributed.
**T11**	TC, PT and TS will be recorded.
**T12**	The third 1/3 of the 75 ml of pre-cooling beverage will be administered.
**T13**	TC, PT and TS will be again evaluated.
**T14**	Ambient temperature, relative humidity, and heat stress and WBGT will be recorded.
**T15**	Participants will start the 15-min warm-up.
**T16**	After the warm-up, TC, PT and TS will be again evaluated.
**T17**	The first 15-min block of the first half will start.
**T18**	TC, PT and TS will be recorded again after the end of the first block.

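### The planned ANOVAs use each session's pre-rinse values as another time level or not at all; prespecifying them as covariates would be a cheap efficiency gain, mainly for lactate and glucose

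*Protocol article*

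**What the plan says.** Table 1 in section 2.4.7 places two sets of measurements before the first rinse at T8, in both sessions. At T5: "Lactate and blood glucose levels are now going to be measured". At T7: "TC, PT and TS are will be measured". Lactate and glucose are repeated once, at T36, which agrees with section 2.4.6.8: "Blood lactate and glucose levels will be measured before and after the protocol". TS, TC and PT are rated 13 more times after rinsing has begun (T9, T11, T13, T16, T18, T20, T22, T25, T27, T29, T31, T33, T35).

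Section 2.7 names three analyses: a one-way repeated measures ANOVA relating condition to the listed outcomes (lactate and glucose among them), a one-way ANOVA for single time points across conditions, and a two-way analysis: "A two-way analysis repeated measures ANOVA will be used to test for within-group effects across time in both conditions". It names no covariate and no change score. It does not list the time levels, and it does not say whether the condition main effect or the condition-by-time interaction answers the trial's question. Baseline data appear there only as descriptive summaries of demographic and clinical characteristics.

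**The concern.** The rinse cannot have changed a value taken before it. If that value is one level of the time factor, the condition main effect averages a true zero with the real effect and shrinks it. If the interaction is used instead, a pre/post outcome is analysed as a raw change score, which carries the full noise of the baseline. If only post values are compared, the baseline is discarded. None of these routes uses the chance difference between a participant's two session baselines to reduce error.

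Power in a trial of 10 to 13 participants is at stake. So is the meaning of the reported condition effect for lactate and glucose, which could be read as a post-session difference when it is half of one.

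**Working it through.** **The plan's own figure.** Section 2.1 uses "a moderate effect size of 0.54" for TS with 90% power and concludes "a total of 10 participants will be needed". The metric is not stated. Read as Cohen's f in a within-participant ANOVA with two measurements, noncentrality is n·m·f²/(1−ρ). With ρ = 0.5, power at n = 10 is 0.859 and n = 12 is needed; with ρ = 0.6, power at n = 10 is 0.923. So 10 can be reached under an f reading. Read as a paired standardised difference, 0.54 needs 39 (two-sided), and power at n = 10 is 33%. Baseline handling enters neither calculation. Below, 0.54 serves only as a common scale, read as a paired standardised difference.

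**Lactate and glucose (one pre, one post).** Let B and Y be the menthol-minus-placebo differences at T5 and T36, each with SD 1 and with correlation r. E(B) = 0 because no rinse has been given and order is randomised; E(Y) = 0.54. The documents do not give r, so I use 0 to 0.7.

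- Main effect: (B+Y)/2 has mean 0.27 and variance (1+r)/2. Standardised effect = 0.27/√((1+r)/2).
- Interaction: Y−B has mean 0.54 and variance 2(1−r). Standardised effect = 0.54/√(2(1−r)).
- Post-only: Y, standardised effect 0.54.
- Adjusted: regress Y on B and test the intercept with n−2 degrees of freedom. Its variance relative to post-only is (1−r²)(n−2)/(n−3).

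| | r = 0 | 0.3 | 0.5 | 0.7 |
|---|---|---|---|---|
| Main effect, standardised | 0.382 | 0.335 | 0.312 | 0.293 |
| Interaction, standardised | 0.382 | 0.456 | 0.540 | 0.697 |
| Adjusted/post-only variance, n = 13 | 1.10 | 1.00 | 0.83 | 0.56 |
| Adjusted/post-only variance, n = 10 | 1.14 | 1.04 | 0.86 | 0.58 |

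Power, two-sided 0.05 (noncentral t; simulation for the adjusted test):

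| | r = 0 | 0.3 | 0.5 | 0.7 |
|---|---|---|---|---|
| n = 13, main effect | 24.5% | 20% | 18% | 16% |
| n = 13, interaction | 24.5% | 33% | 43% | 64% |
| n = 13, post-only | 43% | 43% | 43% | 43% |
| n = 13, adjusted | 40% | 43% | 50% | 67% |
| n = 10, main effect | 19% | 16% | 14% | 13% |
| n = 10, interaction | 19% | 25% | 33% | 50% |
| n = 10, post-only | 33% | 33% | 33% | 33% |
| n = 10, adjusted | 30% | 32% | 38% | 51% |

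Adjusted and post-only have equal variance when r² = 1/(n−2): r = √(1/11) = 0.30 at n = 13 and √(1/8) = 0.35 at n = 10. The change score becomes the more precise of the two once 1+r exceeds 2(n−3)/(n−2): r above 0.75 at n = 10 and above 0.82 at n = 13, outside the range tabulated.

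**TS, TC and PT (one pre, 13 post).** With T7 kept as a level, the main effect is 13/14 = 0.929 of the average post-rinse effect, a dilution of 7%. Assume a correlation of 0.5 between the post-rinse differences. The mean of 13 then has variance (1+12×0.5)/13 = 0.538, and the main effect including T7 has variance (13²×0.538+1+26r)/14². Signal-to-noise relative to post-only, at n = 10:

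| | r = 0 | 0.2 | 0.3 | 0.5 |
|---|---|---|---|---|
| Main effect including T7 | 0.995 | 0.968 | 0.955 | 0.931 |
| Adjusted | 0.935 | 0.972 | 1.025 | 1.278 |

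For these ratings adjustment is worse than the planned main effect at r = 0, about level at 0.2, and better from 0.3.

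**The case against.** A reader might infer that the plan can only use the baseline as a time level. The text does not go that far. Section 2.7 also allows one-way comparisons of single time points, which can be run on post values alone, and the two-way sentence lists neither its outcomes nor its time levels. That part of the objection stands. It does not rescue a two-way analysis of lactate or glucose: with only T5 and T36 available, a time factor must include the baseline. The post-only route avoids dilution but leaves the baseline unused.

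A reader might also infer a serious loss for the primary outcomes. The documents do not support this. The 50% dilution concerns secondary outcomes, the ratings lose 7%, and the interaction is not diluted at all. A chance T7 difference is noise under randomised order, not bias.

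Nor is a gain over a post-only test assured. The crossover already removes stable between-participant differences, so only session-to-session baseline differences can help. T5 and T7 precede exercise in the heat, so r may be low. Even at the larger effect that truly gives 90% at n = 10 (1.155), adjustment at r = 0.5 raises power only from 90% to 93%.

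Finally, it can be said that covariates belong in an analysis plan that is not shown. That would answer a complaint of omission. Here the article states its methods, and those methods have the weakness described.

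**Conclusion.** The point holds as a matter of efficiency and of what the condition effect means. For lactate and glucose, baseline adjustment has more power than both two-way tests at every r tried from 0 to 0.7. At n = 13 the margin over the main effect runs from about 15 to 50 points; over the interaction it is about 15 points at r = 0 and about 3 at r = 0.7. For TS, TC and PT the loss from keeping T7 as a level is small, and any gain from adjustment depends on r.

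The power figures assume a paired standardised effect of 0.54 (which the plan gives for TS, not for lactate or glucose), equal variances, and a correlation that the documents do not report. The planned tests are not invalid, and the stated sample size does not depend on this choice.

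**What to change.** In section 2.7, remove T5 and T7 from the outcome levels. Prespecify the menthol-versus-placebo contrast on post-rinse values with the session's own baseline as covariate.

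- Lactate and glucose: regress the post-session difference (menthol minus placebo) on the T5 difference and test the intercept.
- TS, TC and PT: do the same with a prespecified summary of each session's post-rinse ratings and the T7 difference. Alternatively, fit a mixed model on the post-rinse ratings with condition and the T7 value (centred on the participant's two-session mean) as fixed effects, and with both participant and participant-by-session random effects. The second random effect is essential. With 13 ratings per session and a participant effect alone, simulation under a true null rejected in about 31% to 53% of trials at an assumed within-session correlation of 0.2 to 0.5.

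The change is to wording only. It needs no new data and can be run in SPSS, and the article says the trial has not begun. In the difference regression it uses one error degree of freedom. Against a post-only test it costs about 3 to 4 points of power if r = 0, breaks even at r of about 0.30 to 0.35, and gains above that. If the authors prefer not to adjust, section 2.7 should at least exclude the pre-rinse values from the condition main effect and name the contrast to be tested.

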During football competition in extreme temperatures, players can modify their game in order to maintain performance and prevent fatigue [17], through the flexibility to adjust game intensity, especially when they are “off-the-ball.” Referees, though, have to follow the rhythm of the match and maintain closeness to match events so that correct decisions can be made [18]. Therefore, although previous research showed that the physiological and physical demands of elite-standard football referees are similar to those of a midfield football player [19,20], these demands may increase under more extreme temperatures since they cannot use the same coping strategies [3]. Thus, heat stress may have detrimental effects on performance and sudden or extreme exposure is a major health concern in this population [15,16].

Several thermal (cooling) strategies have been tested and used with the primary goal of reducing central temperature and thermal sensation (TS), and further delaying the onset of hyperthermia-induced fatigue [21]. These can be applied externally (e.g., using a cooling vest, ice pack, cold-water immersion, topically applied menthol) or internally (e.g., ice slurry, crushed ice, cold beverage ingestion, menthol mouth rinsing) [22]. As a matter of fact, ice slurry ingestion has shown to decrease central and brain temperature, and to improve thermal perception via the stimulation of thermoreceptors located within oral and abdominal regions [22,23]. This has led to an increase in the use of this method in professional competitions performed in hot and humid environments [24].

Research on non-thermal internal cooling methods has increased recently, with particular attention to L-menthol, due to its properties in relieving thermal strain associated with exercise in the heat. Menthol oral application stimulates the mandibular and maxillary branches of the trigeminal nerve (which are predominantly responsible for the detection of temperature and nociceptive stimuli across the face and within the oral cavity) and has consistently shown to improve thermal comfort (TC) and decrease TS, which are thought to modulate perceived exertion to improve performance in the heat [24,25].

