### Participants characteristics and eligibility criteria

2.2

Participants meeting the following inclusion criteria will be recruited.1.Highly trained male field football referees registered in the Portuguese Football Federation aged ≥18 and ≤45 years;2.With normal weight (Body Mass Index ≥18.5 and ≤24.9 kg/m^2^);3.Availability to participate in the introductory meeting, familiarization session and 2 experimental sessions;4.Ability to read and agree to sign the informed consent.

Participants with at least one of the following criteria will be excluded from the study.1.Under the influence of any medications that may affect urinary parameters, thermoregulation mechanisms, circulatory system, thyroid and pituitary function or metabolic status;2.Injury, diabetes, autoimmune disease, cardiovascular disease or obstructive disease of the gastrointestinal tract (e.g., diverticulitis, inflammatory bowel disease);3.Schizophrenia, bipolar disorder or other psychotic disorders;4.Diagnosed eating disorders;5.Magnetic resonance imaging (MRI) scans performed within 48 h after familiarization session or any of the experimental trials.

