### Study design, setting and randomization

2.3

A randomized counterbalanced crossover trial with two conditions will be carried out. After passing the eligibility criteria and attending the introductory meeting and a familiarization visit, the participants will be assigned to 2 experimental days for undergoing 2 different randomly ordered experimental conditions. Each condition will be comprised of a 90-min football protocol (SAFT 90) [31], with the administration of one of 2 beverages before warm-up (5 min of pre-cooling) and at the half-time (5 min of per-cooling). There will be a minimum washout period of 7 days between each trial, to reduce carryover effects from the previous condition and to assure an adequate exercise recovery. The trials will take place in an indoor environment, with Wet Bulb Globe Temperature (WBGT) values exceeding 30 °C, at the same time of the day, to control for circadian variations.

After the familiarization visit, the allocation sequence for the order of the experimental conditions will be assigned through individual randomization from a computer-generated random order, equally assigned to every participant, by the main researcher. Randomization will be concealed through a password-protected document that will not be revealed until the first trial. The main researcher will not be blinded in this type of study condition and will have access to the allocation sequence list and will retrieve the randomization code prior to each experimental to prepare the beverages. All the other investigators and the outcomes assessors will be blinded to study condition and group allocation, as well as participants will be blind to the beverages content and aim of the study.

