##### Physical performance

2.4.6.4

Physical performance responses will be measured using 100 Hz accelerometery, with Sonda 4.0 software (StatSports®, London, UK) to estimate total distance, sprint distance, accelerations, and decelerations.

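### The only analysis set in the Statistics section depends on events after randomisation and drops partial sessions, which may bias the menthol–placebo comparison by an unknown amount

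*Protocol article*

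**What the plan says.** Section 2.7 (Statistics) of the protocol article fixes two rules. The first concerns people: "Participants who discontinue or deviate from intervention protocols, and who meet exclusion criteria at some point of the intervention period, will be excluded". The second concerns values: "Missing data will not be included in the statistical analysis". The methods named are one-way and two-way repeated measures ANOVA, plus single time-point comparisons.

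Section 2.2 supplies the criteria that the first rule refers to. They include "Injury, diabetes, autoimmune disease, cardiovascular disease or obstructive disease of the gastrointestinal tract" and an MRI scan within 48 h after the familiarisation session or an experimental trial.

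Section 2.3 sets the timing: "After the familiarization visit, the allocation sequence for the order of the experimental conditions will be assigned through individual randomization". Both experimental sessions follow, so the intervention period lies wholly after randomisation.

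The article describes no all-randomised analysis, no use for data from a session that is stopped early, and no sensitivity analysis on another set.

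**The concern.** Whether a referee enters the analysis depends on what happens to him after he is randomised. In this trial those events may not be neutral. The exercise lasts 90 minutes with "Wet Bulb Globe Temperature (WBGT) values exceeding 30 °C" (section 2.3), and the Introduction says of heat that "sudden or extreme exposure is a major health concern in this population". The Discussion expects oral menthol to raise thermal tolerance and so improve performance. If that is right, stopping early could be more common in one condition and could go with worse values of the outcomes. Accelerometry is used "to estimate total distance, sprint distance, accelerations, and decelerations" (section 2.4.6.4), and an early stop lowers total distance directly.

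Eligibility criteria also become rules for deleting data. An injury during a session would remove what was validly measured before it. An MRI after a session would remove that session's measurements, although they were complete before the scan took place.

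At stake are possible bias in the menthol–placebo difference and loss of information from a very small sample.

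**Working it through.** **1. The plan's own figure.** Section 2.1 needs 10 participants and allows for 30% drop-out: 10 × 1.30 = 13. This reproduces the 13.

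**2. What a 30% loss leaves.** 13 × 0.70 = 9.1 participants on average. With independent losses, the chance that at least 10 remain is the binomial tail P(X ≥ 10 | n = 13, p = 0.70) = 0.218 + 0.139 + 0.054 + 0.010 = 0.42.

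**3. Power at that number.** Section 2.1 does not say what kind of effect size 0.54 is, so two readings are shown, both two-sided at 5%.
- Cohen's f, two conditions, correlation 0.5 (the last two assumed): λ = f² × n × 2 / (1 − 0.5). For n = 13, λ = 0.2916 × 13 × 4 = 15.16 and power is 95%. For n = 9, λ = 0.2916 × 9 × 4 = 10.50 and power is 81%.
- Standardised paired difference: power is 43% with 13 and 30% with 9.

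These figures show only the cost of losing four people. The meaning of 0.54 is a separate matter.

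**4. Ratings at risk.** Table 1 records thermal comfort, thirst and thermal sensation at T7, 9, 11, 13, 16, 18, 20, 22, 25, 27, 29, 31, 33 and 35. That is 14 times per session, or 28 per scale over two sessions. A repeated measures ANOVA over all these times needs all 28 values, so one gap removes the participant.

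**5. What one stopped session costs.** Take, as a hypothetical case, a referee who stops during the fifth 15-minute block (T32) of his second session. He has given 12 ratings per scale in that session (T7 to T31) and 14 in the first. If he is excluded, 12 + 14 = 26 of 28 ratings per scale are discarded, along with his core temperature and heart rate records.

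**6. Bias, as an illustration only.** Assumptions: strain is normally distributed; menthol lowers it by 0.54 SD; the within-person correlation is 0.5 or 0.8; anyone whose strain passes a common threshold in either session is removed from both.

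| Participants excluded | Estimate as share of true effect, correlation 0.5 | Correlation 0.8 |
|---|---|---|
| 10% | 90% | 95% |
| 20% | 83% | 91% |
| 30% | 78% | 88% |

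With 20% excluded, 17–19% pass the threshold on placebo and 7–8% on menthol. Under this mechanism the estimate moves towards no difference. If menthol had no effect, the mechanism would be symmetric and would create none. A different mechanism could reverse the direction, for example if referees who respond poorly to menthol leave more often. None of these inputs comes from the article.

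**The case against.** The strongest reply is that nothing in the article shows heat-related stopping, let alone more of it on placebo. This stands. The 30% in section 2.1 is a general allowance for the whole study, and sections 2.6 and 3 treat the problem as one of retention: travel costs, reminders, contact during wash-out. The participants are highly trained and the course is audio-paced. A reader might infer that heat failures will vanish from the comparison, or that the 30% measures them. The documents support neither.

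A reader might also infer that the rule deletes the very contrast under study. That goes too far. Completion and time to stopping are not listed outcomes. A referee who never returns for the second session adds little to a within-person contrast under any rule. The real loss is narrower: partial data from stopped sessions, and the fact of stopping.

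The exclusion sentence can also be read as requiring both conditions, so that only a participant who discontinues or deviates and also meets an exclusion criterion is removed. The list reading is more natural, but the wording leaves both open. On the narrower reading fewer people are removed by that rule, yet the missing-data rule and the ANOVA's need for complete cases remain.

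Listwise loss should not be given a number from an assumed missing rate per rating. The article gives no such rate, independent gaps are unrealistic when a stop removes a block of ratings, and section 2.7 does not say that all 14 times enter one ANOVA. Single time-point comparisons need only two values per person.

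Finally, CONSORT reporting would make exclusions visible. It would not put those participants back into the comparison.

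**Conclusion.** The concern holds in a limited form. The article itself fixes an analysis set defined by post-randomisation events, and it offers no alternative set and no use for partial sessions. Following it as written discards valid data and may bias the menthol–placebo comparison. The size and direction of that bias are unknown, because they depend on how many participants stop, in which condition and why.

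What can be sized is the loss of numbers. If the plan's own 30% occurs, about 9 of 13 remain and the chance of keeping the required 10 is 42%, assuming independent losses. Any further listwise loss depends on which rating times enter the ANOVA. The conclusion takes the exclusion sentence as a list of separate grounds. It should be corrected before data collection, but it does not by itself invalidate the trial.

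**What to change.** Reword the two sentences in section 2.7.

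- **Analysis set.** Primary: all randomised participants with any outcome data, analysed by allocated sequence, keeping everything collected up to the point of stopping. Requiring some data is itself a post-randomisation condition, so report how many have none, by sequence.
- **Model.** For repeated measures, use a REML linear mixed model with condition, time, condition × time, period and sequence as fixed effects and participant as a random effect. Adding session within participant as a random term avoids treating ratings from one session as independent. The model uses all available ratings and assumes that missing values are missing at random.
- **Early stops.** Report them by condition, with the reason. Total distance in a stopped session is truncated, not missing, so state how it is handled: for example, distance covered to the stop as observed, with a sensitivity analysis.
- **Sensitivity.** Keep the protocol-adherent set as a sensitivity analysis, and reword the exclusion sentence so that it is clear whether its grounds are separate or joint.
- **Eligibility criteria.** Do not use the section 2.2 criteria to delete data already validly collected. This concerns the analysis set only and changes nothing about who may continue in the trial.

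The cost is a short rewording, a little more analysis work, and reliance on missing at random, which the data cannot verify.
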